# Comparison of complementary and alternative medicine with conventional mind–body therapies for chronic back pain: protocol for the Mind–body Approaches to Pain (MAP) randomized controlled trial

**DOI:** 10.1186/1745-6215-15-211

**Published:** 2014-06-07

**Keywords:** Back pain, Cognitive-behavioral therapy, Mindfulness meditation

## Abstract

**Background:**

The self-reported health and functional status of persons with back pain in the United States have declined in recent years, despite greatly increased medical expenditures due to this problem. Although patient psychosocial factors such as pain-related beliefs, thoughts and coping behaviors have been demonstrated to affect how well patients respond to treatments for back pain, few patients receive treatments that address these factors. Cognitive-behavioral therapy (CBT), which addresses psychosocial factors, has been found to be effective for back pain, but access to qualified therapists is limited. Another treatment option with potential for addressing psychosocial issues, mindfulness-based stress reduction (MBSR), is increasingly available. MBSR has been found to be helpful for various mental and physical conditions, but it has not been well-studied for application with chronic back pain patients. In this trial, we will seek to determine whether MBSR is an effective and cost-effective treatment option for persons with chronic back pain, compare its effectiveness and cost-effectiveness compared with CBT and explore the psychosocial variables that may mediate the effects of MBSR and CBT on patient outcomes.

**Methods/Design:**

In this trial, we will randomize 397 adults with nonspecific chronic back pain to CBT, MBSR or usual care arms (99 per group). Both interventions will consist of eight weekly 2-hour group sessions supplemented by home practice. The MBSR protocol also includes an optional 6-hour retreat. Interviewers masked to treatment assignments will assess outcomes 5, 10, 26 and 52 weeks postrandomization. The primary outcomes will be pain-related functional limitations (based on the Roland Disability Questionnaire) and symptom bothersomeness (rated on a 0 to 10 numerical rating scale) at 26 weeks.

**Discussion:**

If MBSR is found to be an effective and cost-effective treatment option for patients with chronic back pain, it will become a valuable addition to the limited treatment options available to patients with significant psychosocial contributors to their pain.

**Trial registration:**

Clinicaltrials.gov Identifier: NCT01467843.

## Background

Identifying cost-effective treatments for chronic low back pain (CLBP) remains a challenge for clinicians, researchers, payers and patients. About $26 billion is spent annually in the United States in direct costs of medical care for back pain [1]. In 2002, the estimated costs of lost worker productivity due to back pain were $19.8 billion [2]. Despite numerous options for evaluating and treating back pain, as well as the greatly increased medical care resources devoted to this problem, the health and functional status of persons with back pain in the United States has deteriorated [3]. Furthermore, both providers and patients are dissatisfied with the status quo [4-6] and continue to search for better treatment options.

There is substantial evidence that patient psychosocial factors, such as pain-related beliefs, thoughts and coping behaviors, can have a significant impact on the experience of pain and its effects on functioning [7]. This evidence highlights the potential value of treatments for back pain that address both the mind and the body. In fact, four of the eight nonpharmacologic treatments recommended by the American College of Physicians and the American Pain Society guidelines for persistent back pain include “mind–body” components [8]. One of these treatments, cognitive-behavioral therapy (CBT), includes mind–body components such as relaxation training and has been found to be effective for a variety of chronic pain problems, including back pain [9-13]. CBT has become the most widely applied psychosocial treatment for patients with chronic back pain. Another mind–body therapy, mindfulness-based stress reduction (MBSR) [14,15], focuses on teaching techniques to increase mindfulness. MBSR and related mindfulness-based interventions have been found to be helpful for a broad range of mental and physical health conditions, including chronic pain [14-19], but they have not been well-studied for chronic back pain [20-24]. Only a few small pilot trials have evaluated the effectiveness of MBSR for back pain [25,26] and all reported improvements in pain intensity [27] or patients’ acceptance of pain [28,29].

Further research on the comparative effectiveness and cost-effectiveness of mind–body therapies should be a priority in back pain research for the following reasons: (1) the large personal and societal impact of chronic back pain, (2) the modest effectiveness of current treatments, (3) the positive results of the few trials in which researchers have evaluated mind–body therapies for back pain and (4) the growing popularity and safety, as well as the relatively low cost, of mind–body therapies. To help fill this knowledge gap, we are conducting a randomized trial to evaluate the effectiveness, comparative effectiveness and cost-effectiveness of MBSR and group CBT, compared with usual medical care only, for patients with chronic back pain.

### Specific aims

Our specific aims and their corresponding hypotheses are outlined below.

1. To determine whether MBSR is an effective adjunct to usual medical care for persons with CLBP

*Hypothesis 1*: Individuals randomized to the MBSR course will show greater short-term (8 and 26 weeks) and long-term (52 weeks) improvement in pain-related activity limitations, pain bothersomeness and other health-related outcomes than those randomized to continued usual care alone.

2. To compare the effectiveness of MBSR and group CBT in decreasing back pain–related activity limitations and pain bothersomeness

*Hypothesis 2*: MBSR will be more effective than group CBT in decreasing pain-related activity limitations and pain bothersomeness in both the short term and long term. The rationale for this hypothesis is based on (1) the modest effectiveness of CBT for chronic back pain found in past studies, (2) the positive results of the limited initial research evaluating MBSR for chronic back pain and (3) growing evidence that an integral part of MBSR training (but not CBT training)—yoga—is effective for chronic back pain.

3. To identify the mediators of any observed effects of MBSR and group CBT on pain-related activity limitations and pain bothersomeness

*Hypothesis 3a*: The effects of MBSR on activity limitations and pain bothersomeness will be mediated by increases in mindfulness and acceptance of pain.

*Hypothesis 3b*: The effects of CBT on activity limitations and pain bothersomeness will be mediated by changes in pain-related cognition (decreases in catastrophizing, beliefs that one is disabled by pain and beliefs that pain signals harm, as well as increases in perceived control over pain and self-efficacy for managing pain) and changes in coping behaviors (increased use of relaxation, task persistence and coping self-statements and decreased use of rest).

4. To compare the cost-effectiveness of MBSR and group CBT as adjuncts to usual care for persons with chronic back pain

*Hypothesis 4*: Both MBSR and group CBT will be cost-effective adjuncts to usual care.

We will also explore whether certain patient characteristics predict or moderate treatment effects. For example, we will explore whether patients with higher levels of depression are less likely to improve with both CBT and MBSR or whether such patients are more likely to benefit from CBT than from MBSR (that is, whether depression level is a moderator of treatment effects).

## Methods/Design

### Overview

We are conducting a randomized clinical trial in which individuals with CLBP are randomly assigned to group CBT, a group MBSR course or usual care alone (Figure 1). Participants will be followed for 52 weeks after randomization. Telephone interviewers masked to participants’ treatment assignments will assess outcomes 4, 8, 26 and 52 weeks postrandomization. The primary outcomes we will assess are pain-related activity limitations and pain bothersomeness. Participants will be informed that the study researchers are comparing “two different widely used pain self-management programs that have been found helpful for reducing pain and making it easier to carry out daily activities”.

**Figure 1 F1:**
[figure not shown]
**Flowchart of the trial protocol.** CBT, Cognitive-behavioral therapy; MBSR, Mindfulness-based stress reduction.

The protocol for this trial has been approved by the Human Subjects Review Committee of the Group Health Cooperative (250681-22). All participants will be required to give their informed consent before enrollment in this study.

### Study sample and setting

The primary source of participants for this trial will be the Group Health Cooperative (GHC), a group-model, not-for-profit health-care organization that serves over 600,000 enrollees through its own primary care facilities in Washington state. As needed to achieve recruitment goals, direct mailings will be sent to persons 20 to 70 years of age living in the areas served by the GHC.

### Inclusion and exclusion criteria

We are recruiting individuals from 20 to 70 years of age whose back pain has persisted for at least 3 months. The inclusion and exclusion criteria were developed to maximize the enrollment of appropriate patients while screening out patients who have low back pain of a specific nature (for example, spinal stenosis) or a complicated nature or who would have difficulty completing the study measures or interventions (for example, psychosis). Reasons for exclusion of GHC members were identified on the basis of (1) automated data recorded (using the *International Classification of Diseases*, *Ninth Revision* coding system), during all visits over the course of the previous year and (2) eligibility interviews conducted by telephone. For non-GHC members, reasons for exclusion were identified on the basis of telephone interviews. Tables 1 and 2 list the inclusion and exclusion criteria, respectively, as well as the rationale for each criterion and the information sources.

**Table 1 T1:** Inclusion criteria

**Inclusion criteria**	**Rationales**	**Sources**
Primary sources		A, TI
All GHC members with at least one primary care visit for back pain within the previous 3 to 15 months	Initial targeting of members with back pain visits in recent past is an efficient method of identifying persons with chronic back pain.	
Random sample of GHC members without visits for back pain within the previous 3 to 15 months	Emphasis placed on recruitment of GHC members to obtain complete treatment utilization and cost data from GHC medical records	
GHC members responding to an ad in the GHC magazine		
Secondary sources		A, TI
Random samples of nonmembers of GHC living in Washington state	Nonmembers of GHC included to ensure that recruitment goals are met.	
Age range 20 to 70 years	Chronic back pain in children is a result of causes different from those we will study.	
	Adults have a higher risk of undiagnosed serious conditions that cause back pain.	
Nonspecific, uncomplicated back pain as defined by ICD-9 codes (for primary source only: GHC members with primary care visits for back pain in the previous 3 to 15 months)	These codes are consistent with low back pain that is nonspecific and uncomplicated.	A
724.2 Lumbago		
724.5 Backache, unspecified		
724.8 Other symptoms referable to back		
846.0-9 Sprains and strains, sacroiliac		
847.2 Sprains and strains, lumbar		
847.3 Sprains and strains, sacral		
847.9 Sprains and strains, unspecified site of the back		

GHC, Group Health Cooperative; ICD-9, *International Classification of Diseases*, *Ninth Revision*. A, Automated data gathered from visits; TI, Telephone interview.

**Table 2 T2:** **Exclusion criteria**^
**a**
^

**Exclusion criteria**	**Rationales**	**Sources**
Patient claims visit was not for low back pain	Study restricted to low back pain	TI
Low back pain has lasted <3 months	Low back pain not chronic	TI
Self-rated bothersomeness of pain rating of <4 (on 0 to 10 scale) and pain interference with activities rating <3 (on 0 to 10 scale) during previous week	Back pain too mild to detect improvement	TI
Abdominal aneurysm	Back pain due to or possibly result of specific disease or condition	A
Cancer in previous 5 years, other than basal cell or squamous cell cancer of the skin		A, TI
Discitis		A
Degenerative disc disease		A
Fracture of vertebra		A, TI
Infectious cause of back pain		TI
Pregnancy		TI
Scoliosis, severe or progressive		A, TI
Spinal stenosis		A, TI
Spondylolisthesis		A, TI
Back surgery within previous 2 years	Back problem is complicated by medical or medicolegal issues	TI
Seeking or receiving compensation for back pain or involved in litigation related to back pain		
Blindness	Condition might make it difficult to attend the classes or practice at home	A
Deafness		A
No way to play home practice audio recordings at home		TI
Paralysis		A
Psychoses, major		A, TI
Schedules do not permit participation in classes or home practice (including planning to move out of town)		TI
Vision problems, severe		TI
Hearing problems, severe		TI
Lack of transportation		TI
Fibromyalgia	Condition or circumstance might confound treatment effects or interpretation of data	TI
Rheumatoid arthritis and/or anklyosing spondylitis		A, TI
Other disabling chronic conditions (for example, disabling heart or lung disease, diabetic neuropathy, receiving treatment for hepatitis)		TI
Planning on seeing a specialist for back pain (for example, surgeon, neurologist, rheumatologist)		TI
Dementia	Condition would make it difficult to provide fully informed consent	A
Unable to read or speak English		TI
Currently taking a mind–body class for back pain or class taken within previous 1 year	Possible bias due to current or recent interventions	TI

^a^A, Automated data gathered from visits; TI, Telephone interview.

In addition, we require that participants be willing and able to attend the CBT or MBSR classes during the 8-week intervention period if assigned to one of those treatments, and to respond to the four follow-up questionnaires so that we can assess outcomes.

### Recruitment procedures

Because the study intervention involves classes, we are recruiting participants in ten cohorts consisting of up to forty-five individuals each. We are recruiting participants from three main sources: (1) GHC members who have made visits to their primary care providers for low back pain and whose pain has persisted for at least 3 months, (2) GHC members who have not made a visit to their primary care provider for back pain but who are between the ages of 20 and 70 years and who respond to our nontargeted GHC mailing or our ad in GHC’s twice-yearly magazine and (3) community residents between the ages of 20 and 70 years who respond to a direct mail recruitment postcard.

For the targeted GHC population, a programmer will use GHC’s administrative and clinical electronic databases to identify potentially eligible members with a visit in the previous 3 to 15 months to a provider that resulted in a diagnosis consistent with nonspecific low back pain. These GHC members are mailed a letter and consent checklist that explains the study and eligibility requirements. Members interested in participating sign and return a statement indicating their willingness to be contacted. A research specialist then calls the potential participant to ask questions; determine eligibility; clarify risks, benefits and expected commitment to the study; and request informed consent. After informed consent has been obtained from the individual, the baseline telephone assessment is conducted.

For the nontargeted GHC population (that is, GHC members without visits with back pain diagnoses received within the previous 3 to 15 months but who could possibly have low back pain), a programmer uses administrative and clinical electronic databases to identify potentially eligible members who were not included in the targeted sample described in the preceding paragraph. This population also includes GHC members who respond to an ad in the GHC magazine. The same methods used for the targeted population are then used to contact and screen the potential participants, obtain their informed consent and collect baseline data.

With regard to community residents, we have purchased lists of the names and addresses of a randomly selected sample of people living within our recruitment area who are between 20 and 70 years of age. The people on the list are sent direct mail postcards describing the study including information regarding how to contact study staff if interested in participating. Once an interested person has contacted the research team the same process detailed above is followed.

To ensure that all initially screened study participants remain eligible at the time the classes begin, those who consent more than 14 days prior to the start of the intervention classes will be recontacted approximately 0 to 14 days prior to the first class to reconfirm their eligibility. The primary concern is to exclude persons who no longer have at least moderate baseline ratings of pain bothersomeness and pain-related interference with activities. Those individuals who remain eligible and give their final informed consent will be administered the baseline questionnaire.

### Randomization

After completing the baseline assessment, participants will be randomized in equal proportions to the MBSR, CBT or usual care group. Those randomized to the MBSR or CBT group will not be informed of their type of treatment until they arrive at the first classes, which will occur simultaneously in the same building. The intervention group will be assigned on the basis of a computer-generated sequence of random numbers using a program which ensures that allocation cannot be changed after randomization. To ensure balance on a key baseline prognostic factor, randomization will be stratified based on our primary outcome measurement instrument: the modified version of the Roland Disability Questionnaire (RDQ) [30,31]. We will stratify participants into two activity limitations groups: moderate (RDQ score ≤12 on a 0 to 23 scale) and high (RDQ scores ≥13). Participants will be randomized within these strata in blocks of varying size (three, six or nine) to ensure a balanced but unpredictable assignment of participants. During recruitment, the study biostatistician will receive aggregated counts of participants randomized to each group to assure that the preprogrammed randomization algorithm is functioning properly.

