### Statistical analyses

#### Primary analyses

In our comparisons of treatments based on the outcome measures, we will analyze outcomes assessed at all follow-up time points in a single model, adjusting for possible correlation within individuals and treatment group cohorts using generalized estimating equations [89]. Because we cannot reasonably make an assumption regarding constant or linear group differences over time, we will include an interaction term between treatment groups and time points. We plan to adjust for baseline outcome values, sex and age, as well as other baseline characteristics found to differ significantly by treatment group or follow-up outcomes, to improve precision and power of our statistical tests. We will conduct the following set of analyses for both the continuous outcome score and the binary outcome (clinically significant change from baseline), including all follow-up time points (4, 8, 26 and 52 weeks). The MBSR treatment will be deemed successful only if the 26-week time point comparisons are significant. The other time points will be considered secondary evaluations.

We will use an intent-to-treat approach in all analyses; that is, the assessment of individuals will be analyzed by randomized group, regardless of participation in any classes. This analysis minimizes biases that often occur when participants who do not receive the assigned treatments are excluded from analysis. The regression model will be in the following general form:

$$\begin{array}{ll} g\left(y_{t}\right)= & \beta_{0}+\beta_{1}\left(\mathrm{baseline}\right)+\alpha_{1}\left(\mathrm{treatment}\right)+\alpha_{2}\left(\mathrm{time}\right)\\ & +\alpha_{3}\left(\mathrm{treatment}\right)\times \mathrm{time}+\alpha_{4}z+\epsilon , \end{array}$$

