where *y*_t_ is the response at follow-up time *t*, *baseline* is the prerandomization value of the outcome measure, *treatment* includes dummy variables for the MBSR and CBT groups, *time* is a series of dummy variables indicating the follow-up times and *z* is a vector of covariates representing other variables adjusted for. (Note that α_1_, α_2_, α_3_ and α_4_ are vectors.) The referent group in this model is the usual care group. For binary and continuous outcomes, we will use appropriate link functions (for example, logit for binary). For each follow-up time point at which the omnibus *χ*^2^ test is statistically significant, we will go on to test whether there is a difference between MBSR and usual care to address aim 1 and a difference between MBSR and CBT to address aim 2. We will also report the comparison of CBT to usual care. When determining whether MBSR is an effective treatment for back pain, we will require that aim 1, the comparison of MBSR to usual care, must be observed.

On the basis of our previous back pain trials, we expect at least an 89% follow-up and, if that holds true, our primary analysis will be a complete case analysis, including all observed follow-up outcomes. However, we will adjust for all baseline covariates that are predictive of outcome, their probability of being missing and differences between treatment groups. By adjusting for these baseline covariates, we assume that the missing outcome data in our model are missing at random (given that baseline data are predictive of missing data patterns) instead of missing completely at random. We will also conduct sensitivity analysis using an imputation method for nonignorable nonresponses to evaluate whether our results are robust enough to compensate for different missing data assumptions [90].

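### Baseline RDQ stratifies the randomisation but is not a pre-specified covariate in the bothersomeness and secondary-outcome models; name it in every model

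*Protocol article*

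**What the plan says.** **Allocation** (Randomization section). The article states that "randomization will be stratified based on our primary outcome measurement instrument: the modified version of the Roland Disability Questionnaire (RDQ", and gives balance on an important prognostic factor as the reason. The two strata are "moderate (RDQ score ≤12 on a 0 to 23 scale) and high (RDQ scores ≥13". Allocation inside each stratum uses blocks whose size varies between 3, 6 and 9, and "participants will be randomized in equal proportions to the MBSR, CBT or usual care group".

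**Fixed model terms** (Statistical analyses, Primary analyses). "We plan to adjust for baseline outcome values, sex and age". The notes to the model equation say that the baseline term "is the prerandomization value of the outcome measure". So each model carries the baseline of its own outcome, and RDQ is there by rule only when RDQ is the outcome.

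**Further terms.** The same section adds "other baseline characteristics found to differ significantly by treatment group or follow-up outcomes". Its paragraph on missing data says that "we will adjust for all baseline covariates that are predictive of outcome", and goes on to mention the probability of being missing and differences between treatment groups. Neither baseline RDQ nor its stratum is named in either place.

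**The concern.** A factor used to constrain allocation is normally carried into the analysis. Stratified blocks make the treatment estimate less variable when the stratifier is prognostic. A linear model without the stratifier does not credit that gain: its residual variance still contains the between-stratum part, so the reported standard error is somewhat too large and the test somewhat conservative.

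The RDQ models are safe because baseline RDQ is a fixed term there. The gap is in bothersomeness, a co-primary outcome, and in the secondary outcomes. There, inclusion depends on a selection step made after the data are seen, and one of its two routes is nearly closed. A factor balanced by design will rarely differ significantly between arms, which leaves the route through prediction of the outcome. The sentence in the missing-data paragraph is also unclear on whether a covariate must meet all the listed conditions or any one of them. Under the all-conditions reading, a balanced stratifier would tend to fail.

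At stake are a little precision in the continuous analyses, a little power in the logit analyses, and one avoidable discretionary choice in a co-primary analysis.

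**Working it through.** **Inputs from the article** (Sample size and detectable differences): 264 evaluable participants, 88 per group; bothersomeness responders 47.5% v 69.3% with 80% power; bothersomeness SD 2.4; two-sided 5% level; 11% loss to follow-up.

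**Input assumed:** r, the partial correlation of the RDQ stratum with follow-up bothersomeness given the fixed covariates. The article says only that bothersomeness is correlated with measures of function, which is a marginal statement. I take r from 0.1 to 0.3.

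**Step 1: the plan's own figures.** The two-proportion formula for 47.5% v 69.3% at 80% power gives 80 per group, or 88 with continuity correction, as planned. Recruitment: 264/(1 − 0.11) = 296.6, so 297. The sizing reproduces without any covariate adjustment.

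**Step 2: interval width, continuous bothersomeness.** Half-width without the stratum = 1.96 × 2.4 × √(2/88) = 0.709. With the stratum it is 0.709 × √(1 − r²), so omission widens the interval by the factor 1/√(1 − r²). If the standard error is too large by that factor, the true size of a nominal 5% test is P(|Z| > 1.96/√(1 − r²)).

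| r | Half-width with stratum | Widening if omitted | Power for 1.1 points, omitted → included | True size of 5% test if omitted |
|---|---|---|---|---|
| 0 | 0.709 | 0% | 86.0% → 86.0% | 5.0% |
| 0.1 | 0.706 | 0.5% | 86.0% → 86.3% | 4.9% |
| 0.2 | 0.695 | 2.1% | 86.0% → 87.3% | 4.5% |
| 0.3 | 0.676 | 4.8% | 86.0% → 89.0% | 4.0% |

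The 86.0% is at 88 per group. The article's 90% for 1.1 points is approached at 99 per group (89.7%). That is a separate matter; only the change in power counts here.

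**Step 3: simulation.** For each r, 4,000 three-arm trials of 264 were simulated with stratified blocks of 3, 6 or 9 and a linear model containing the outcome's own baseline.

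| r | Model SE, stratum omitted | Model SE, included | Ratio | Observed SD of estimate, omitted | Type I error, omitted | Stratum significant at 5% |
|---|---|---|---|---|---|---|
| 0 | 0.3318 | 0.3318 | 1.000 | 0.3285 | 4.8% | 5% |
| 0.1 | 0.3318 | 0.3301 | 1.005 | 0.3267 | 4.7% | 37% |
| 0.2 | 0.3321 | 0.3253 | 1.021 | 0.3205 | 4.0% | 91% |
| 0.3 | 0.3321 | 0.3168 | 1.048 | 0.3212 | 4.3% | over 99% |

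The SE ratios match Step 2. The observed SDs carry Monte Carlo error of about 1/√8000 = 1.1%, and the error rates about √(0.05 × 0.95/4000) = 0.3 percentage points, so small differences between rows should not be read closely.

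**Step 4: size in participants.** If RDQ is never included, the equivalent is 264/(1 − r²) − 264 = 2.7, 11 and 26 at r = 0.1, 0.2 and 0.3. Weighting roughly by the chance that a 5% screen misses the stratum: 0.63 × 2.7 = 1.7; 0.09 × 11 = 1.0; under 0.01 × 26 = under 0.3.

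**Step 5: the logit analyses.** The primary comparison is the proportion with at least 30% improvement, with logit as the example link. The formula in Step 2 is for linear models and does not carry over. In logistic regression, omitting a prognostic covariate pulls the odds ratio towards 1 relative to the conditional one and costs some power; it does not widen the log-odds interval.

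**The case against.** The plan largely protects itself. Omitting the stratifier costs something only if it predicts the outcome, and prediction of the outcome is the plan's own trigger for adding a covariate. Since the Randomization section already regards RDQ as prognostic, its selection is likely. Full covariate lists are also commonly left to an analysis plan, which is not shown here, and the allocation and analysis sections do not contradict each other.

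Much of this stands. At r = 0.2 or more the stratum was significant in at least 91% of simulated trials. At r = 0.1 it was significant in only 37%, but there the cost is about 0.5% in width. The objection does not remove the point, because the article is not silent: it gives an equation and a list of fixed covariates, and the stratifier is not among them outside the RDQ models. Selection through a later screen, with one route nearly closed and one sentence ambiguous, is a weaker commitment than naming the term.

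A reader might infer something stronger: that bothersomeness intervals are bound to be wider than the design allows, that as many as 26 participants' worth of information is lost, and that this erodes the 80% power for that outcome. The documents do not support this. Widening needs two conditions, prediction beyond the outcome's own baseline and failure of the screen. The 26 is an upper bound at an assumed r of 0.3, where the screen almost always adds RDQ. The 80% belongs to the binary comparison and reproduces from an unadjusted formula. Stratified allocation still lowers the true variance of the estimate whether or not the model includes the stratum; it is the reported standard error that is conservative.

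**Conclusion.** The point holds as a minor mismatch between design and analysis. The stratification factor is not pre-specified in the models for co-primary bothersomeness and the secondary outcomes; it enters only if a data-driven rule selects it. If it is prognostic beyond the outcome's own baseline and is not selected, continuous-outcome intervals may be about 0.5% to 5% too wide for r of 0.1 to 0.3, and the logit analyses may lose a little power through attenuation. Mean differences are unbiased and the false-positive rate is not inflated.

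The sizes rest on the assumed r and on a linear model at a single time point with independent residuals. They do not reproduce the planned generalised estimating equations across four follow-ups with clustering by class cohort.

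**What to change.** State that baseline RDQ, either as a continuous score or as the ≤12/≥13 stratum, is a pre-specified covariate in every outcome model, binary and continuous, regardless of any significance screen. In the RDQ models the existing baseline term already does this if the continuous score is chosen.

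The cost is one line in the analysis plan and about one degree of freedom. Table 4 shows RDQ collected at baseline, and randomisation cannot proceed without it, so no new data are needed. Recruitment ended in April 2014 and the article appeared in June 2014, less than 26 weeks later, so at publication the line could still be added before the primary-endpoint data were complete.
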